## Abstract

**Background:**

Witnessing and experiencing violence impedes children’s healthy development and learning, inhibits positive relationships, provokes low self-esteem and emotional distress, and can lead to self-harm and aggressive behavior across the life course. Evidence-based programs are needed that incorporate violence prevention strategies alongside methods to improve wellbeing and healthy development for children and their families. This trial evaluates the Responsible, Engaged, and Loving Fathers (REAL Fathers) intervention, a Ugandan-led multilevel community-based mentoring program for young fathers (ages 16–25) with children below the age of three years.

**Methods:**

To assess the REAL Fathers intervention, we use a cluster-randomized controlled trial design within 48 sub-counties randomly sampled from 24 districts in six regions of Uganda. Sub-counties were randomly allocated to treatment or control arms at baseline. Study participants are fathers ages 16–25 years and their cohabitating wives whose eldest child is below the age of 3 years (*n* = 3744 couple dyads). Primary outcomes are the following: (1) reduced intimate partner violence; (2) reduced violent discipline of children; (3) increased father-child engagement and play; (4) improved early childhood development. Secondary outcomes include the following: (1) father’s knowledge of and (2) attitudes towards positive parenting and discipline; (3) father’s use of positive parenting and discipline; (4) father’s use of emotional engagement with child; (5) couple communication and conflict resolution; (6) gender equitable household and caregiving decision-making and behaviors; (7) father engagement in child health-promoting activities; (8) improved knowledge of family planning methods; (9) reduced unmet need for family planning; (10) reduced problem alcohol use; and (11) supportive community norms for father-child engagement and play. Longitudinal survey data will be collected by trained enumerators using KoboCollect in six local languages at three time points: one month before the intervention (baseline); one month after the intervention (endline); and nine months after the intervention (follow-up). Intervention effects on primary and secondary outcomes will be assessed using difference-in-differences (DiD) mixed-effects models that account for the clustered design.

**Discussion:**

This trial will examine the impacts of a multilevel community-based intervention for young fathers and their families in Uganda on positive parenting, childhood development, and violence reduction. Overall, successful completion of this study will contribute to the evidence-based on context-informed multilevel approaches that reduce harm and promote wellbeing in families with very young children.

**Trial registration:**

ClinicalTrials.gov #NCT06100679. Registered on October 24, 2023. https://clinicaltrials.gov/study/NCT06100679.

## Administrative information

Note: the numbers in curly brackets in this protocol refer to SPIRIT checklist item numbers. The order of the items has been modified to group similar items (see http://www.equator-network.org/reporting-guidelines/spirit-2013-statement-defining-standard-protocol-items-for-clinical-trials/).

## Introduction

### Background and rationale {6a}

Violent discipline—the use of physical and psychological aggression by caregivers to punish children—and intimate partner violence (IPV) are globally the most common forms of violence experienced by children and women, respectively [1–3]. In sub-Saharan Africa, it is estimated that nearly 9 in 10 (86%) of children between the ages of 1 and 14 years have experienced violent discipline by a caregiver in the past month [4]. In Uganda, there is high prevalence among caregivers of preferences for physically harsh discipline, relative to less violent forms of child discipline [5]. Data from Uganda’s latest Demographic and Health Survey reflect these discipline preferences, indicating that 85% of children aged 1 and 14 years experienced violent discipline in the past month [6]. IPV is also common in Uganda, with nearly three in five (58%) of Ugandan women and over two in five (44.5%) of Ugandan men report experiencing some form of IPV victimization by a spouse or partner in their lifetime [6]. IPV and violent child discipline commonly co-occur in households [7, 8], with both of these forms of violence associated with immediate and long-term harms to children’s development and wellbeing [9–11]. Meta-analyses suggest a causal relationship between violence against children (VAC), witnessing parental IPV, and increased risk of experiencing and perpetrating IPV in adulthood [12–15], suggesting intergenerational linkages in violence perpetration.

We apply social network, social norms, and social learning theory to understand the ways in which VAC and IPV behaviors intersect [16–18]. These theories jointly posit that violence is learned behavior, modeled by important individuals within peer groups, families, and communities [19, 20]. For example, empirical evidence has shown that violence is “socially contagious” and clusters within households [21, 22]. Previous work in Uganda shows that both boys and girls who witnessed and experienced violence in their homes had between 3.23 (95% CI 1.99 to 5.24) and 8.12 (95% CI 5.15 to 12.80) times the odds of using physical or sexual violence themselves [23]. Exposure to physical punishment during childhood is correlated with perpetration of similar practices toward one’s own children later in life [14, 24]. Studies confirm multiple ways that VAC and IPV intersect, including the following: shared risk factors such as gender inequality and marital conflict; social and gender norms that condone violence and promote masculinities based on violence and control; clustering of VAC and IPV within the same households; intergenerational transmission; and shared consequences of VAC and IPV on social, emotional, and physical wellbeing [8, 22]. These consequences include harms to the following: physical and mental health [25]; cognitive, social-emotional, and behavioral development [26]; and educational outcomes [27].

Given the many intersections between IPV and VAC, a growing literature has examined coordinated responses to prevent the two forms of violence [28, 29]. Emerging evidence indicates the importance of parenting programs to address violence against children and women [30]; however, few parenting programs explicitly seek to reduce both IPV and VAC in joint programming, and many either focus solely on female caregivers or find it challenging to recruit and retain male caregivers [31, 32]. Working with both female and male parents and caregivers capitalizes on the important role that fathers play in shaping positive child development outcomes, including social, emotional, and cognitive development [33, 34]. Engaging both caregivers also contributes to the transformation of restrictive and harmful social and gender norms that are known shared risk factors for both IPV and VAC [35]. Further, in addition to reducing and preventing IPV and VAC incidence, there is a need to strengthen protective factors against later-in-life harms and intergenerational cycles of violence [36]. Parent–child connectedness and attachment, as well as healthy and empathic communication between intimate partners, are increasingly recognized as protective factors against intergenerational IPV and VAC [37–39].

#### The REAL Fathers Intervention

This trial seeks to evaluate the Uganda-based intervention known as Responsible, Engaged and Loving Fathers (REAL Fathers), a multilevel social and behavior change intervention that trains community-based mentors to work with young fathers (ages 16–25 years) and their female partners on positive parenting and communication skills-building [40]. The intervention’s mentors hold home-based individual mentoring and community-based group mentoring sessions with young fathers and spouses, alongside project-level community engagement opportunities. The intervention is designed to address common antecedents of VAC and IPV, including harmful social and gender norms, or the unwritten rules, values, and expectations of individuals within a community that condone violence, promote gender inequality and discrimination, and promote masculinities based on violence and control [8, 41]. The intervention components are grounded in social learning theory [42] and social cognitive theory of gender development and differentiation [43]. The REAL Fathers intervention uses modeling of alternative strategies for nonviolent discipline and conflict resolution to improve fathers’ parenting and communication skills and confidence in adapting nonviolent strategies, with related shifts in gender norms to expand the socially acceptable behaviors available to men as they self-regulate to adhere to gender roles and expectations in their communities.

From its inception, REAL Fathers has drawn upon cross-sector partnerships to address community needs and to promote scale and sustainability. The intervention was developed by communities in Northern Uganda in partnership with Save the Children and Georgetown University [40]. Piloted in 2013 in post-conflict northern Uganda (Amuru District), it was proven effective in reducing violence via mentorship on positive parenting, non-violent discipline, and gender equity and respectful couple communication [40]. REAL Fathers was subsequently scaled in additional areas of the Northern Region (Nwoya, Gulu, and Nakapiripirit) in 2020, with the involvement of the original program designers, implementers, and researchers. In this same period, funding was also provided to identify stakeholders and mechanisms to adapt, scale, and implement REAL Fathers in Uganda-based early childhood development (ECD) programs and centers. In January 2022, the Government of Uganda endorsed REAL Fathers as an implementation strategy in support of its third National Development Plan (NDP III 2021–2025) and related early childhood development policies and frameworks. With this endorsement and government buy-in, the partnership submitted and was awarded a grant to scale REAL Fathers to reach 280,000 fathers and 425,000 children from 2023–2027 in six new regions across Uganda: Ankole, Buganda, Bunyoro, Busoga, Lango, and Teso. It is not feasible or desired to reach the planned number of beneficiaries (i.e., fathers and children) simultaneously (i.e., all at once). As such, there will be five rounds of REAL Fathers implementation over the course of the four-year project. As depicted in Table 1, we will embed this present trial into the current scale-up of REAL Fathers, using a subsample of fathers involved in the wider intervention.

**Table 1 Tab1:**
[figure not shown]
Mapping of trial assessment periods on REAL Fathers implementation cohorts

### Objectives {7}

The present trial aims to test the effectiveness of the REAL Fathers intervention in reducing rates of family violence and improving child wellbeing and development outcomes in six regions of Uganda that have not yet received the REAL Fathers intervention. We hypothesize that, as compared to study participants in the waitlist control group who receive standard care, participants in the intervention group will see improvements in the primary and secondary outcome measures (as listed below). Activity inputs, mechanisms of action, outputs, and outcomes are summarized in Fig. 1 (*Theory of Change—end of document*).

**Fig. 1 Fig1:**
[figure not shown]
REAL Fathers behavior theory of change

### Trial design {8}

The impact of the REAL Fathers intervention will be assessed using a cluster-randomized controlled trial (cRCT) wait-list control rollout design [44]. This cRCT employs a superiority framework to test the null hypothesis that there will be similar differences in the primary and secondary outcomes from baseline to endline in both the REAL Fathers intervention group and the waitlisted control group receiving standard care [45]. The survey questionnaire will use validated questions, as piloted in a previous evaluation of the intervention [40], and will be extended to include items from Caregiver Reported Early Development Instruments (CREDI) [46] and socio-demographic items adapted to the local context. The phased rollout of the study will involve three cohorts, each with 1872 father-spouse dyads in the control group and 1,872 father-spouse dyads in the intervention group, for a total of 3744 father-spouse dyads across the three cohorts and study arms. Baseline data collection will occur roughly one month before the start of a cohort, with endline data collection occurring roughly 8 months later (i.e., one month after the 7-month mentoring period of the REAL Fathers intervention ends). Follow-up data collection will occur 8 months after endline data collection. This rollout design is optimal for resource constraint and ethical considerations. The trial is designed to match the speed of implementation, with a random sample of study participants in the intervention group selected from the overall implementation cohorts. Due to personnel and resource constraints in reaching the large number of program beneficiaries, staggered implementation of the intervention—and therefore also the cRCT trial which uses a sub-sample of program beneficiaries—is necessary. Further, from an ethical standpoint, in order to offer those in the control conditions of the study an opportunity to participate in REAL Fathers, several implementation cohorts are necessary, making this wait-list control rollout design the most appropriate for the study context.

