Based on the Uganda Bureau of Statistics 2019 population projections and Uganda Demographic and Health Survey 2016 data, only 4% of the male population (16–25 years) are young fathers who are married or cohabiting [6]. According to the latest Uganda population and housing census, the average village size is about 100 households [49]. Thus, no more than 10 young men (16–25 years) will be fathers whose eldest child is below the age of three years. To be on the conservative side, we assume that, on average, only 8 young fathers are eligible for the study from any given village. Let $$\overline{m }$$ denote this average and suppose *cv* is the coefficient of variation in the number of fathers across the different villages, and ρ is intra-cluster correlation (ICC). Pilot studies on the REAL Fathers intervention approximated ICC of 0.20–0.24 at the village level. Thus:$$Deff=\left(1+\left(\left({cv}^{2}+1\right)\overline{m }-1\right)\rho \right)=\left(1+\left(\left(0.063+1\right)\times 7-1\right)\right)\times 0.20=2.3$$

Based on the above parameters and an attrition rate of 10% between the baseline and endline, a total of 1872 couple dyads is required per study arm (3744 in total). This translates to 156 couples per district: 78 in each study arm from 6 villages; and 312 couples per geographical region. This makes an assumption of treatment effect size of 10% on indicators at project level and 80% statistical power and 95% certainty (alpha = 0.05).

The study is being conducted across regions characterized by diverse subcultures, both between and within locations. To ensure sufficient power to detect potential heterogeneity in treatment effects across key subcultural groups, we adjusted the sample size accordingly. Drawing on pilot data, we anticipate a moderate level of effect heterogeneity across these subcultures. According to Ford and Norrie (2016) [50] and Kent et al. (2018) [51], moderate heterogeneity corresponds to a coefficient of variation (CV) of approximately 20% in treatment effects. To account for this, we increased the originally planned sample size by 20%, resulting in a target of 2200 participants per study arm.

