47	Soroti	Tubur	Intervention
48	Soroti	Asuret	Control

A total of 3744 young fathers and their spouses (i.e., couple dyads) will be recruited (1872 per study arm) for this study, or 156 young fathers and their spouses per district. Study participants will be recruited solely through household visits. All young fathers and their spouses willing to follow the study protocol will go through an informed consent process. In a first step, fathers who meet the study’s eligibility criteria will be contacted and briefly informed about the study and invited for an interview. If consent is obtained, the young father’s female partner (either his spouse or cohabitating girlfriend) will be informed about the study and invited for an interview either on the same day or at a later scheduled date. If both the young father and the female partner agree to take part in the study, written informed consent will be obtained from both.

If the couple is not available on the initial day of contact, up to two additional attempts (for a maximum of three visits) will be made to contact the couple on varying days of the week. If the couple declines to participate or cannot be located after the third visit, a new young father will be randomly selected from the village listing. We will use randomization without replacement to reach the required sample.

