### Interim analyses {21b}

We will conduct interim DID regression analyses on the primary and secondary outcomes at the endline and follow-up time periods of Cohort 1 and Cohort 2. Final analyses will be conducted on the full dataset after the end of the intervention for all study cohorts (i.e., after Cohort 3 endline and again at Cohort 3 follow-up).

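### Trial design gives each of three cohorts 1872 dyads per arm, yet totals 3744 across all cohorts; the per-cohort figure is three times too large if 3744 is the trial total

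*Protocol article*

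**What the plan says.** Trial design {8} describes "three cohorts, each with 1872 father-spouse dyads in the control group and 1,872 father-spouse dyads in the intervention group, for a total of 3744". The same sentence defines the scope of the total: "3744 father-spouse dyads across the three cohorts and study arms".

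Other sections treat 3744 as the size of the whole trial:
- Abstract, Methods: "3744 couple dyads", in "48 sub-counties randomly sampled from 24 districts".
- Sample size {14}: "a total of 1872 couple dyads is required per study arm (3744 in total"), followed by "This translates to 156 couples per district: 78 in each study arm from 6 villages; and 312 couples per geographical region".
- Recruitment {15}: "A total of 3744 young fathers and their spouses (i.e., couple dyads) will be recruited (1872 per study arm) for this study".

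Two other statements bear on the number. Sample size {14} closes with a target of 2200 per arm, after a 20% increase for effect heterogeneity. Data management {19} sets a quality-control sample of about 1%, given as 37 respondents, at each round of data collection.

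Cohorts are also units of analysis. Interim analyses {21b} plans "interim DID regression analyses on the primary and secondary outcomes at the endline and follow-up time periods of Cohort 1 and Cohort 2", and Methods for additional analyses {20b} plans hierarchical models for each trial cohort.

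**The concern.** The only sentence that gives a cohort size contradicts its own total. The other sections settle which total is likely, but not how many dyads or sub-counties belong to each cohort. Table 6 schedules enrolment, baseline and randomisation separately for each cohort, while Table 7 lists a single allocation of 48 sub-counties with no cohort column. A reader cannot tell whether a cohort uses all 48 sub-counties or only some.

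Two things are at stake. Field quotas per cohort cannot be taken from the text, and Trial status says enrolment is active. Also, anyone reading a Cohort 1 or Cohort 2 interim result against this sentence would credit it with the sample of the whole trial.

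**Working it through.** **Step 1. The trial total.** Inputs: 1872 per arm, 156 couples per district and 78 per arm per district (Sample size {14}); 24 districts and 48 sub-counties (abstract).
- 2 × 1872 = 3744
- 24 × 156 = 3744
- 48 × 78 = 3744

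The whole-trial total is reproduced three ways. (The 312 couples per region is a per-arm figure: 4 × 78 = 312 and 6 × 312 = 1872. That is a separate wording matter.)

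**Step 2. The sentence as printed.** 3 cohorts × 2 arms × 1872 = 11,232, and 11,232 / 3744 = 3.0. The sentence can hold only if 1872 per arm is the sum over the cohorts.

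**Step 3. Can the sample-size formula decide?** n = 2(Z + Z_power)² P̄(1 − P̄) / (P1 − P0)² × Deff, with P0 = 0.40, P1 = 0.50, P̄ = 0.45, 80% power (0.8416), Deff = 2.3 and 10% attrition.
- Z = 2.2414 (upper tail 0.0125): 470.5 × 2.3 = 1082.1; / 0.9 gives 1203 per arm.
- Z = 2.4977 (two-sided 0.0125): 552.0 × 2.3 = 1269.6; / 0.9 gives 1411 per arm.

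Neither gives 1872, so the formula cannot show whether 1872 is per cohort or overall.

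**Step 4. The two other figures.**
- Quality control: 37 / 3744 = 1.0%. For a cohort of 3744 / 3 = 1248 dyads, 37 would be 3.0%. The stated 1% fits either 3744 dyads in each cohort's round, or a round counted over all three cohorts. The text does not say which.
- 2200 per arm is 4400 in total, which is not 3744.

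**Step 5. Illustration of cohort-level power.** Assumption, not in the document: three equal cohorts, so 1872 / 3 = 624 per arm. Approximate power = Φ(0.1 × √(n_eff / 0.495) − Z), where n_eff = n × 0.9 / Deff and 0.495 = 2 × 0.45 × 0.55.

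| n per arm | Deff | n_eff | 0.1√(n_eff/0.495) | Power, Z = 2.24 | Power, Z = 2.50 |
|---|---|---|---|---|---|
| 1872 | 2.3 | 732.5 | 3.847 | 95% | 91% |
| 624 | 2.3 | 244.2 | 2.221 | 49% | 39% |
| 624 | 1.72 | 326.5 | 2.568 | 63% | 53% |
| 733 (2200 / 3) | 2.3 | 286.8 | 2.407 | 57% | 46% |

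The Deff of 1.72 supposes that the same villages recur in every cohort. With 78 couples from 6 villages there are 13 per village, or 4.33 per cohort. The plan's own expression with cv² = 0.063 and ICC 0.20 then gives 1 + (1.063 × 4.33 − 1) × 0.20 = 1.72. If different villages are used in each cohort, 2.3 may hold or may be too low. The rows illustrate; they are not bounds.

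**The case against.** The strongest reply is that this is a misplaced phrase in one sentence. The end of that sentence, the abstract, Sample size and Recruitment all point to 3744, and no estimand, test or randomisation step changes. This stands as far as the trial total goes: the pooled final analysis is not harmed if 3744 is right.

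A second reply is that a journal article may leave the per-cohort split to the full protocol or analysis plan. That also stands. The missing split alone would be no finding. The fault is that the article does state a cohort size, and the stated size cannot be right alongside its total. Table 1 is not shown, but its caption describes assessment periods rather than sample sizes.

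Three stronger readings are tempting, and the document does not support them:
- **That the plan claims 80% power for each cohort.** Sample size {14} ties its power statement to project level, and Interim analyses {21b} claims no power.
- **That cohort analyses have 40–50% power on the plan's own inputs.** This needs an equal split and an unchanged Deff of 2.3. Neither is stated for cohorts, and other plausible inputs move the figure above 60%.
- **That a null Cohort 1 result would drive programme changes.** The section on modifying interventions {11b} attributes changes between cohorts to responsive feedback mechanisms, and the Discussion to experience and lessons learned. Neither names the interim regression results.

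**Conclusion.** The sentence is wrong as written. It implies 11,232 dyads and states 3744. If 3744 is the whole-trial total, as the abstract, Sample size, Recruitment and the district arithmetic indicate, the per-cohort figure is overstated by a factor of three. That inference is strong but not complete, because the 2200-per-arm target and the 1% quality-control figure remain unreconciled with it.

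This is more than a slip of style, since it misstates a sample size that planned cohort-level analyses depend on. Actual cohort sizes cannot be derived from the text; 624 per arm is only an average under an equal split. The power figures show that a single cohort could fall well short of the pooled design, but they are conditional on that split and on the design effect.

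**What to change.** 1. Correct the Trial design sentence to say that 1872 dyads per arm (3744 in all) is the total over the three cohorts, if that is what is meant.
2. State the actual number of dyads per arm and of sub-counties in each cohort. Only the sponsor can supply these.
3. Reconcile the corrected numbers with the 2200-per-arm target in Sample size {14} and with the 37-respondent, 1% per-round sample in Data management {19}, saying what a round covers.
4. State that the 80% power refers to the pooled analysis and that the Cohort 1 and Cohort 2 interim estimates are descriptive.

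Do not enter 624 per arm or any cohort-level power from the illustration as fixed values. The cost is protocol wording only. Nothing in the randomisation or the final analysis changes, provided 3744 is confirmed as the total.
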